| **Purpose** | ○ **Primary purpose:**  - Analysis of the effect of using a smartphone app-based human coaching program on the patient's symptoms and quality of life in patients who underwent gastrectomy for stage 1 gastric cancer  - Comparison of food restriction scale scores of EORTC QLQ STO22 at 3 months after surgery in patients who used smartphone app and patients who received nutrition counseling  ○ **Secondary purpose:**  - Comparison of food restriction scale scores of EORTC QLQ C30 and STO22 at 6 months after surgery  - Comparison of food restriction scale scores of EORTC QLQ C30 and STO22 at 12 months after surgery  - Meal volume, biomarkers (BMI, muscle mass, etc.), blood test results | | | | |
| **Background** | - Patients who underwent gastrectomy suffer from symptoms such as abdominal pain, diarrhea, nausea/vomiting, increased pulse, weakness, and hypoglycemia (gastric resection syndrome) after a meal due to the resection of the pylorus that controls the speed of food movement between the stomach and small intestine. Symptoms are especially severe when the patient rushes to eat food, eats a large amount at once, and eats high-sugar foods.  - During the hospitalization period, the patient begins with Mieum and proceeds with a small amount of porridge, but after discharge, he suffers trial and error because he does not know how to proceed in his daily life. In addition, after being diagnosed as a cancer patient, people around them listen to unverified stories and eat mainly with certain foods, or they may not be able to consume enough nutrition due to restrictions on certain foods. Sometimes suffered.  - Currently, a smartphone app (Noom) that provides a 1:1 personalized coaching service is being used among the general public to keep a daily meal diary and calculate meal calories for weight loss. Noom not only makes it easy for users to enter the food eaten during the day based on the food database, but also helps the coach in charge check daily to keep the dietary control.  - If a gastric cancer patient uses Noom in the process of nutritional adaptation after surgery, coaching can be performed at an appropriate time according to the patient's situation. As a result, patients and their caregivers are expected to reduce trial and error related to dietary adaptation and reduce gastrectomy syndrome. | | | | |
| Results of  previous study | □ Absent ☑ Present  - In the past literature, the results that weight control and metabolic syndrome control were significantly improved when using a smartphone app were published in several papers.  - There have also been studies showing that breast cancer survivors, which are highly related to obesity, lose weight, increase vegetable intake, and increase exercise volume when nutritional control using a smartphone app is used.  - Regarding stomach cancer, a study on improving lung capacity with a mobile self-monitoring tool has been published, and a protocol has been introduced for studies related to nutrition or diet.  **< Pilot study>**  ○ Title: Investigation of the effectiveness of QOL improvement using a smartphone app-based human coaching program in patients who underwent gastrectomy for stage 1 gastric cancer.  ○ Research content: Patients who underwent gastrectomy for stage 1 gastric cancer receive individual coaching using a smartphone app on health management methods after gastrectomy such as weight, diet, and exercise for 3 months from the date of discharge. EORTC QLQ questionnaire was answered at 1 and 3 months after gastrectomy, and satisfaction with human coaching was surveyed. The patient's body count and nutritional results on blood tests are also collected.  ○ Patient enrollment  -Enrollment period: 2019.9.19. ~ 11.6  -Number of enrolled patients (Actual/Planned): 20/20 (100%)  -Number of drop-out: 6/20 (30%)  -Reason of drop-out:  -Diagnosed as stage 2 or higher in the final pathology examination (n=4)  -Refusal (n=2)  ○ Results  1) Eating restriction score of EORTC QLQ-STO22  -Preoperative, median value: 6.7 (IQR 6.7, 13.3)  -Postoperative 1 month, median value: 30.0 (IQR 13.3, 56.7)  -Postoperative 3 month, median value: 20.0 (IQR 3.3, 26.7)  2) Satisfaction:  : The use of the app helped adapt to the diet and the overall satisfaction was very high.  -Ease of use of the app – Strongly yes (9), yes (3), no (1)  -Ease of understanding of the information provided - Strongly yes (8), yes (4)  -Usability of using the app - Strongly yes (12), yes (1)  -Appropriateness of time spent in app - Strongly yes (8), yes (5)  -Overall satisfaction: Strongly yes (11), yes (2) | | | | |
| **Study overview** | ○ Study design: single center, prospective, randomization  ○ Research participation period: One year after gastrectomy for early gastric cancer  ○ Data collection period: IRB approval day – 2021. 12. 31  ○ Overall study period: IRB approval day – 2022. 6. 30. | | | | |
| **Data collection items and**  **Clinical test items** | ○ Demography: age, sex, name initial  ○ Anthropometric information: height, body weight, body component such as muscle mass measured with a body composition analyzer  ○ Past medical history: past medical history, smoking, alcohol, concomitant medications  ○ Diagnostic, pathological data: operating day, operation method, pathological results of gastric cancer, postoperative complications  ○ Laboratory findings: Hemoglobin, Protein, Albumin, Cholesterol  ○ Questionnaires: EORTC QLQ C30, STO22 | | | | |
| **Research participation condition** | ☑inpatient ☑outpatient □ local residents □ others | | | | |
| **Inclusion criteria** | 1. Patients over 19 years of age  2. Patients diagnosed with stage 1 gastric cancer before surgery  (Early gastric cancer at preoperative endoscopy or stage I at CT scan)  3, Patients scheduled to undergo distal or total gastrectomy  4. Patients who are able to use the smartphone app or a care giver living with him can use the app to actively intervene in the patient's life.  5. Patients who have written research consent | | | | |
| **Exclusion criteria** | 1. Vulnerable patients (pregnancy, a person who lacks the ability to speak)   2. Patients who cannot use the smartphone app or the active intervention of a care-giver is difficult | | | | |
| **Drop-out criteria** | 1. Patients who have not undergone distal gastrectomy or total gastrectomy 2. The pathology test result is stage II or higher after gastrectomy 3. Patients who need adjuvant chemotherapy after gastrectomy   4. The hospital stay exceeds 3 weeks due to complications  5. Patients request withdrawal of participation  6. Patients having difficulty in collecting data suitable for the purpose of the study because they have not visited at all 1, 3, 6, and 12 months | | | | |
| **Study method** | - Patients who are scheduled to undergo gastrectomy for stage 1 gastric cancer are randomly assigned either to the mHealth group or the face-to-face counseling group. Patients in the mHealth group (N=90) will use mobile application for 3 months after discharge and those who in the face-to-face counseling group (N=90) will receive general nutrition counseling at 1 month and 3 months after gastrectomy.  - QOL, body component, and nutritional outcomes will be compared between the two groups.  - When obtaining the consent form, the mHealth group will be provided with a simple noom instruction manual and a noom meal record guide, and will be informed of how to use it.  - In addition, individual coaching will be given through articles and messengers on how to manage post-gastrectomy such as weight, diet, and exercise on the mobile app for 3 months from the discharge date.  - Survey response on quality of life at outpatient visits 1, 3, 6, 12 months after surgery  [figure not shown]  * The allowable date of visit at 1, 3, 6, and 12 months after surgery is 1 month before and after. | | | | |
| **Intervention method** | **- mHealth group:** After being discharged from hospital, patients will receive coaching using a smartphone app for 3 months. When the patient is discharged from the hospital, he downloads the Noom app on his or her mobile phone, registers, and then uses the Noom program. In addition, a personal coach is assigned to provide appropriate coaching to the patient on the app.  **-Face-to-Face group:**　Patients will receive individual nutrition counseling from a clinical nutritionist at the hospital at 1 month and 3 months after surgery. | | | | |
| **Evaluation** | Between the mHealth and face-to-face groups  - Comparison of scores of EORTC QLQ-C30 and STO22 at 1, 3, 6, and 12 months postoperatively.  - Comparison of meal amount at 1, 3, 6, and 12 months postoperatively.  - Comparison of body component (BMI, muscle mass, etc) at 1, 3, 6, and 12 months postoperatively.  - Comparison of nutritional outcomes (hemoglobin, albumin, protein, cholesterol) at 1, 3, 6, and 12 months postoperatively | | | | |
| **Number of research subjects** | - In the results of the pilot study, the eating restriction score of EORTC QLQ-STO22 that was answered at 1 month postoperatively was 30 points. The drop-out rate of the entire study was 30%. Based on this, the following hypothesis was established.  - Among the EORTC STO22 items that patients in the mHealth group responded to 1 month after surgery, the score for the eating restriction item was expected to be 30±10 (mean±standard deviation). The item score for the control group was expected to be 35 points.  - alpha value: 0.05  - power: 80%  → sample size was calculated as 65 cases in each group.  → Considering 30% of drop-out rate, a total of 180 cases (90 cases in each group) is needed.  - If drop-outs are more than expected, the number of sample size can be adjusted through statistical advice. | | | | |
| **Statistical consideration** | **1. Randomization**  - Randomization generally performs permutated mixed block randomization, and is generated in a 1:1 ratio using 2 and 4 mixed block blocks. Using the nQuery Program, a randomly assigned table is created according to the stratification factor and notified through a web-based clinical research management system.  - Stratification factors: extent of gastrectomy (distal vs. total gastrectomy)  2. **Statistical analyses**  - Patient's clinical characteristics are expressed as mean ± standard deviation or ratio using descriptive statistics.  - Significance was evaluated by t-test for continuous variables and Chi-square test for discontinuous variables.  - For the values ​​repeatedly measured at time intervals, the difference between the two groups was compared using a mixed effect model. | | | | |
| **Specimen** | ☑Not applicable | | | | |
| **Plan for secondary use of collected data** | □ Not applicable  □ Use of personal information including personally identifiable information  ☑ Use of personal information except personally identifiable information  □Use of specimen | | | | |
| **Monitoring plan** | ○ This study is conducted through the use of smartphone apps and questionnaires of the subjects, and safety issues are not applicable.  ○ Adverse reactions are not collected because there are no adverse reactions in the use of smartphone apps or surveys. | | | | |
| **Ethical consideration** | ○ Protection measures for vulnerable research subjects ⍌ Not applicable  ○ How to use personal information including personally identifiable information  - Personally identifiable information: hospital registration number, name, telephone number, birth year  - Personal information: age, sex, height, weight, past medical history, smoking status, alcohol consumption, concomitant medication use, operation date, surgical method, gastric cancer pathology result, postoperative complications, BMI, body composition analysis and body measurement results, Hb, Protein , Albumin, Cholesterol  - Purpose of using personal information, including personally identifiable information:  Search of medical record, smartphone app use and human coaching  - Use period of personal information including personally identifiable information:  (1) Stored for 3 years after the end of the study  (2) When a participant requests deletion of personal information, it will be deleted immediately  ○ Personal Information Protection Plan  - Subjects have the right to refuse consent to collection and use of personal information, and participation in this study is restricted if consent is rejected (Article 15 of the Personal Information Protection Act, collection and use of personal information), and minimum personal information necessary for the purpose of the study (Article 16 of the Personal Information Protection Act, Restriction on Collection of Personal Information). Records related to personal information will be kept for 3 years from the time the research is completed in accordance with Article 15 of the Enforcement Rule of the 「Life Ethics and Safety Act」. This past document will be destroyed (Article 21 of the Personal Information Protection Act, destruction of personal information).  - Disposal plan for data after research is completed: Research data including personal information will be disposed of as follows in accordance with Article 16 of the Enforcement Decree of the Personal Information Protection Act after the storage period.  (1) Information stored in the form of electronic files is permanently deleted in a way that cannot be restored through initialization or overwriting to prevent data from being restored.  (2) Written printed materials are completely destroyed through a shredder.  - The PI oversees the disposal process and ensures that the material has been completely destroyed.  - Protection methods for research subjects and to ensure confidentiality of personal information  (1) Only the minimum personal information necessary for the purpose of this study will be collected, and the collected personal identification information and personal information will not be leaked or shared with others other than the responsible researcher and researcher  (2) Data will be managed by assigning a research ID, and the information collected for research will be stored as an electronic file with a password in a locked laboratory. Only PI and researchers can access the research file.  (3) It will be permanently deleted by PI after storage for 3 years after the end of the study.  ○ Damage compensation plan: Not applicable  ○ Support matters for research subjects: □Absent ☑Present  - Free use of smartphone app (Noom) for 3 months  - Nutrition education at 1 month and 3 months after surgery  ○ Additional costs incurred when a research subject participates in the research:  ☑Absent □Present  ○ Data management plan  (1) Data is managed by assigning a research ID, and information collected for research is stored in an electronic file with a password in a locked laboratory.  (2) Research files can only be accessed by PI and researchers, and collected documents are kept in a lockable drawer to limit access.  (3) The collected data is stored for 3 years after the end of the study and then permanently disposed of by the lead researcher.  (4) The identifier code associated with the subject's personal information is restricted by PI by storing it in a lockable chest of drawers. | | | | |

※ “Personal identification information” refers to information that can identify an individual, such as the name and resident registration number of a research subject.

※“Personal information” refers to personal information, such as personal identification information, genetic information, or health information.

**1. Background**

**(1) Changes in the diet of patients after gastrectomy**

- Patients who underwent gastrectomy experience the following anatomical changes.

[figure not shown]
- Patients suffer from gastrectomy syndrome due to resection of the pylorus, which regulates the speed of food movement between the stomach and small intestine. Gastric resection syndrome includes abdominal pain, diarrhea, nausea/vomiting, increased pulse, weakness, and hypoglycemia that occur after eating.

- In particular, when the patient rushes to eat or eats a large amount of food, and eats high-sugar foods, gastrectomy syndrome can be severely experienced.

**(2) Dietary adaptation of the patient**

- Patients receive nutritional counseling during the hospitalization period, but when they return to their daily life after discharge, there is no separate education on how to eat and how to adjust, resulting in various trials and errors.

- In particular, after being diagnosed as a cancer patient, there are cases where people around us hear unverified stories and eat mainly with certain foods, or they may not be able to consume enough nutrition due to restrictions on certain foods.

- They are also not well aware of postgastrectomy syndrome, so they constantly experience discomfort after eating.

- This postgastrectomy syndrome is most severe in the early postoperative period and gradually relieves after dietary adaptation.

(3) **Diet management using a smartphone app**

[figure not shown]
- Currently, for weight loss, a smartphone app (Noom) is being used that keeps a daily meal diary, calculates meal calories, and provides 1:1 customized coaching service.

- Noom not only makes it easy for users to enter the food eaten during the day based on the food database, but also helps the coach in charge check daily to keep the dietary control.

- If Noom is used in the process of dietary adaptation after surgery for gastric cancer patients, it is expected that balanced nutritional intake will be achieved through appropriate dietary disorders. In addition, by providing information on gastrectomy syndrome, it is possible to reduce and prevent gastrectomy syndrome.

- Also, as Noom actively encourages exercise therapy, the patient is motivated for proper exercise.

- This is expected to reduce the patient's symptoms and improve the quality of life.

(4) **Previous literature review**

- In the past literature, the results that weight control and metabolic syndrome control were significantly improved when using a smartphone app were published in several papers.

- There have also been studies showing that breast cancer survivors, which are highly related to obesity, lose weight, increase vegetable intake, and increase exercise volume when nutritional control using a smartphone app is used.

- Regarding stomach cancer, a study on improving lung capacity with a mobile self-monitoring tool has been published, and studies related to nutrition or diet have only been introduced with protocols so far.

[figure not shown]

<Hanna et la, Effect of early and intensive nutrition care, delivered via telephone or mobile application, on qaulity of life in people with upper gastrointestinal cancer: study protocol of a randomized controlled trial, BMC Cancer, 2018>

**(5) Results of pilot study**

**- Research title**

: Investigation of the effectiveness of QOL improvement using a smartphone app-based human coaching program in patients who underwent gastrectomy for stage 1 gastric cancer.

**- Research content**

√ Target patient: Patients who underwent gastrectomy for stage 1 gastric cancer

√ Human Coaching Program Usage Period: 3 months from discharge date

√ Study method: Before discharge, the patient installs an app for the human coaching program on his/her smartphone and is informed of how to use it. After discharge, you receive individual coaching on how to manage your health after gastrectomy such as weight, diet, and exercise using a smartphone app.

√ Outcomes:

- EORTC QLQ questionnaire performing at 1 and 3 months postoperatively.
- Satisfaction with using the app
- Weight, BMI, body component
- Nutritional parameters (Hb, protein, albumin, cholesterol)

**- Patient enrollment**

√ Period of enrollment: 2019.9.19. ~ 2019.11.6

√ Number of enrolled patients (Actual/Planned): 20/20 (100%)

√ Number of drop-out: 6/20 (30%)

√ Reason of drop-out:

- Diagnosed as stage 2 or higher in the final pathology examination (n=4)

- Refusal (n=2)

**- Results**

1) Eating restriction score of EORTC QLQ-STO22

-Preoperative, median value: 6.7 (IQR 6.7, 13.3)

-Postoperative 1-month, median value: 30.0 (IQR 13.3, 56.7)

-Postoperative 3-month, median value: 20.0 (IQR 3.3, 26.7)

2) Satisfaction (n=13)

: The use of the app helped adapt to the diet and the overall satisfaction was very high.

-Ease of use of the app – Strongly yes (9), yes (3), no (1)

-Ease of understanding of the information provided - Strongly yes (8), yes (4)

-Usability of using the app - Strongly yes (12), yes (1)

-Appropriateness of time spent in app - Strongly yes (8), yes (5)

-Overall satisfaction: Strongly yes (11), yes (2)

(6) **Benefit**

- Evaluation of whether dietary management using a smartphone app contributes to improving the patient's quality of life in patients undergoing gastrectomy

- Development of coaching materials for patients undergoing gastrectomy

**2. Study Objectives**

**(1) Primary endpoint:**

- Analysis of the effect of using a smartphone app-based human coaching program on the patient's symptoms and quality of life in patients who underwent gastrectomy for stage 1 gastric cancer

- Comparison of food restriction scale scores of EORTC QLQ C30 and STO22 at 1 month after surgery between the patients who used smartphone app and those who received nutrition counseling

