**(2) Secondary endpoints:**

- Food restriction scale score at 3, 6, 12 months after operation

- Meal amount (total calories, nutrient amount)

- Body component (body weight, body mass index, muscle mass, body fat percentage)

- Nutritional outcomes (hemoglobin, protein, albumin, cholesterol)

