**(5) Outcome parameters**

- Comparison of food restriction scale score of EORTC QLQ C30, STO22:

Whether there is a significant difference in the mean value is evaluated by the p-value of the t-test. Since the 1st month questionnaire is the primary endpoint, it is evaluated individually and the significance of the mixed model's p-value is evaluated to see if there are overall differences in the values ​​measured several times.

- Inbody values ​​such as meal volume, BMI, muscle mass, and blood tests were compared with the average value at 3 months, and the significance was evaluated by the p-value of the mixed model to see if there was a difference overall.

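### The protocol names 3 months as the primary time point in the synopsis Purpose row but 1 month in sections 2 and 7(5), and names the questionnaire inconsistently; one primary endpoint must be fixed throughout.

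*Protocol*

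**What the plan says.** The primary comparison is described in several places.

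- **Synopsis, Purpose row, primary:** "Comparison of food restriction scale scores of EORTC QLQ STO22 at 3 months after surgery in patients who used smartphone app". The secondary list there covers 6 and 12 months, for example "Comparison of food restriction scale scores of EORTC QLQ C30 and STO22 at 6 months after surgery". It does not mention 1 month.
- **Section 2(1), primary endpoint:** "Comparison of food restriction scale scores of EORTC QLQ C30 and STO22 at 1 month after surgery".
- **Section 2(2), secondary endpoints:** "Food restriction scale score at 3, 6, 12 months after operation".
- **Section 7(5), outcome parameters:** under the item "Comparison of food restriction scale score of EORTC QLQ C30, STO22", the protocol says "Since the 1st month questionnaire is the primary endpoint, it is evaluated individually", by t-test. A mixed model then looks for an overall difference across visits.
- **Sample size (synopsis row on number of subjects, repeated in section 6(2)):** planned on the STO22 eating-restriction score at 1 month, with a mean of 30 and SD of 10 in the mHealth group against 35 in the control group, alpha 0.05 and 80% power. This gives 65 per group, raised to 90 per group (180 in total) for 30% drop-out.
- **Synopsis, Evaluation row, and section 7(2):** both questionnaires compared at 1, 3, 6 and 12 months, with no ranking.

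**The concern.** The same 3-month comparison is primary in one current section and secondary in another, so this is more than loose paraphrase. The questionnaire also varies: STO22 alone in the Purpose row and the sample size, QLQ-C30 together with STO22 in sections 2(1) and 7(5).

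The plan has one alpha of 0.05 and a sample size for one comparison. With two time points each described as primary, a reader of the results could not say from the protocol which test decides whether the trial succeeded. If the choice could be made after the data were seen, the 5% error rate would no longer hold. A separate analysis plan cannot cure this by itself, because whichever time point it adopted would contradict part of the protocol.

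**Working it through.** **1. The passages side by side**

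| Place | Primary time point | Questionnaire | Status of 3 months |
|---|---|---|---|
| Synopsis, Purpose row | 3 months | STO22 | primary |
| Synopsis, sample size | 1 month | STO22 | not used |
| Section 2(1) and 2(2) | 1 month | QLQ-C30 and STO22 | secondary |
| Section 6(2), sample size | 1 month | STO22 | not used |
| Section 7(5) | 1 month | QLQ-C30 and STO22 | in the repeated-measures comparison |

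Only the Purpose row says 3 months. Every eating-restriction score that the protocol reports or plans on, in the pilot results and in the sample size, comes from STO22.

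**2. Reproducing the sample size**

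Inputs from section 6(2): difference 35 − 30 = 5, SD 10, alpha 0.05 (sidedness not stated), power 80%.

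n per group = 2(1.960 + 0.842)² × 10² / 5² = 62.8, so 63. The t-based version gives 63.8, so 64. The stated 65 is within two patients. A one-sided test would give 50, so the plan is evidently two-sided.

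Drop-out: 63 / 0.7 = 90 per group, which matches the 180. Starting from 65, it would be 65 / 0.7 = 92.9, so 93. The 90 per group leave 90 × 0.7 = 63 evaluable, with power 80.1% (79.5% by the t calculation). The figure therefore reproduces, for STO22 at 1 month only.

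**3. Error rate if either time point could be claimed**

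With two two-sided tests at 0.05 and correlation ρ between the statistics, the chance of at least one false positive is 1 − P(|Z₁| < 1.96 and |Z₂| < 1.96).

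| ρ (assumed) | Chance of at least one false positive |
|---|---|
| 0 | 1 − 0.95² = 9.75% |
| 0.5 | 9.1% |
| 0.7 | 8.3% |
| 0.9 | 7.0% |

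The protocol gives no correlation between the 1-month and 3-month scores, so the range is what can be stated. Keeping both as alternative primaries with alpha split to 0.025 each would need 77 evaluable per group. That is 77 / 0.7 = 110 per group, 220 in total, if the 5-point difference and SD 10 applied at both visits.

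**4. Whether the stated size carries over to 3 months**

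It cannot be shown. The protocol gives no 3-month difference and no 3-month planning SD. The only 3-month information is the pilot median of 20.0 with IQR 3.3 to 26.7, from about 14 patients (20 enrolled, 6 dropped out) in one arm.

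As an illustration only, IQR / 1.349 = 23.4 / 1.349 gives an SD near 17.3. If the 5-point difference is carried over, which is an assumption, n = 2(1.960 + 0.842)² × 17.3² / 5², about 189 evaluable per group against 65 stated. The approximation assumes normality, and these data are visibly skewed.

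**The case against.** The best defence is that the document is lopsided rather than evenly split. Sections 2(1), 2(2) and 7(5) and both sample-size paragraphs agree on 1 month, and section 7(5) says it outright: "Since the 1st month questionnaire is the primary endpoint". Only one synopsis row disagrees, and the sample size in the same synopsis contradicts that row. It looks like one uncorrected line. This largely stands. It makes 1 month the more probable intention, but it does not remove the conflict, because no passage says which text prevails.

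Three stronger readings are tempting, and the document does not support them.

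- **Two primaries of equal standing.** A reader might infer this from the two headings. The weight of the text is on 1 month. Nor does the omission of 1 month from the Purpose row mean that the synopsis ignores it: its Evaluation row and its sample size both use it.
- **Four competing tests.** Reading QLQ-C30 and STO22 at two time points as four independent tests would give 1 − 0.95⁴ = 18.5%. The protocol shows no eating-restriction score from QLQ-C30, and scores from the same patients would not be independent. Naming QLQ-C30 is loose wording to correct and does not justify that figure.
- **That 3 months is the better choice, at no cost.** The control group would have had a counselling session by then, and the pilot spread is smaller than at 1 month. But 3 months has no planning inputs, and the illustration above shows that the present size may not serve it. Section 1(2) also says that symptoms are worst soon after surgery, which supports an early assessment. The choice belongs to the sponsor.

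**Conclusion.** The contradiction is real, lies in current text and concerns the definition of the primary endpoint. It must be corrected. Its size is a rise in the false-positive chance from 5% to between about 7.0% and 9.75%, conditional on the time point being open to choice after the data are seen and on assumed correlations from 0.9 to 0. Nothing in the document shows that such a choice is intended.

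The stated sample size supports only the STO22 comparison at 1 month, and only under its own inputs. The pilot IQR at 1 month (13.3 to 56.7) implies by the same rough rule an SD near 32 rather than 10. That is a separate question about the planning SD, and this point does not rest on it.

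**What to change.** Before any comparative data are seen, name one primary endpoint, the STO22 eating-restriction score at one time point, and state it identically in the synopsis Purpose row, the synopsis sample-size row and sections 2(1), 2(2), 6(2) and 7(5). Remove QLQ-C30 from the primary and keep its scores among the secondary comparisons.

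- **If 1 month (simplest):** correct the Purpose row so that 1 month is primary and 3, 6 and 12 months are secondary, and take QLQ-C30 out of the primary in sections 2(1) and 7(5). Section 2(2) and both sample-size paragraphs already fit. The stated 65 per group and 180 in total stay as they are under their own inputs. The cost is a wording amendment.
- **If 3 months:** move 1 month to secondary in sections 2 and 7(5), rewrite both sample-size paragraphs with a justified 3-month difference and SD, and restate the power that 180 patients deliver. The cost cannot be fixed from the protocol, and more patients may be needed.
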